### Feasibility

As the senior exercise park initiative is a new concept to the Australian older community, feasibility will be assessed and will be defined as the number of participants recruited and retained over the recruitment period, overall adherence and seasonal adherence, safety and adverse effects and number of sessions cancelled due to unfavourable weather conditions. In addition, the qualitative data collected via interviews of EPIG participants will be taken into account for feasibility purposes as they might more clearly show participants’ perceptions of this kind of initiative.

Overall adherence to the exercise program will be defined by the number of sessions attended: 100 % adherence if participant attended 35 sessions or 9 sessions of social meetings. EPIG or CG participants’ participation and attendance will be recorded via a spreadsheet diary and will be collected respectively by the exercise supervisor of that participant on each specific session or by the principal researcher. Physical activity calendars will be used to monitor if EPIG or CG participants have participated in any other physical activities during their participation in the study. Reasons for participants missing sessions will be documented on the spreadsheet diary. Participants will be given a phone call in case they miss two consecutive sessions without any communication with any exercise supervisors.

Considering that the exercise sessions are held outdoors, this study intends to investigate if the participants’ adherence would be influenced by weather conditions during the four seasons in Melbourne. Seasonal adherence will be recoded as adherence over Summer (December to end of February), Fall (March to end of May), Winter (June to end of August) and Spring (September to end of November). Also, the number of sessions that were cancelled due to rainy, windy and excessively hot days (above 37 °C) will be recorded given that these conditions would potentially put participant’s safety and health in risk.

Safety and adverse effects will be measured by the number of falls incidents that occur during exercise sessions, and will be recorded via an incident report form (treatment needed post-incident and related lesions or injuries). The circumstances surrounding the fall (e.g. muscle fatigue, dizziness) will be recorded. EPIG participants will be also asked in the following session (48 h) to report if they experienced any uncomfortable delayed muscle soreness or fatigue post-exercise that limited them from doing their daily tasks such as ascending and descending stairs, rising from a chair, and carrying shopping bags. The following question will be used: “Did you experience any muscle soreness after the session that limited you from doing your normal daily activities such as carrying shopping bags, rising from a chair or putting a t-shirt on?”. If they answer “yes” the muscle soreness event will be recorded on the participant’s spreadsheet diary.

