### Recruitment and randomization

Participants will be recruited from Melbourne suburbs. Local senior organizations, retirement villages, community centres, senior clubs and associations in the areas around the park location will be contacted for recruitment purposes. Participants will be also recruited via community health promotion events and advertisement in local newspapers, magazines and online social networking media. Participants will be informed about the project by posters placed in healthcare facilities and places with high circulation of senior citizens and mail-out advertisements to health care practitioners in Melbourne. Participants will be randomly allocated to one of the following groups: (1) Exercise Park Intervention Group (EPIG) or (2) Control Group (CG). Block randomization stratification by gender will be undertaken, so that blocks of 12 participants will be recruited at a time, randomized into one control group of six participants and one exercise groups of six participants (Fig. 1). To accommodate couples (e.g. partners/married couples) participation, randomisation by couple will also take place. Assessors will prepare the envelopes with six paper codes (three exercise intervention and three control group) which will be added to opaque not concealed envelopes. There will be three envelopes: one for couples, one for females and one for males. Participants will be asked to pick one paper from their respective envelope and the picked paper will assign the participant to either the exercise intervention group or control group. Recruitment will be undertaken over a period of 14 months to achieve a sample size of 60 participants in each group. Assessors and participants will not be blinded to their respective group allocation (EPIG or CG).

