**Fig. 1 Fig1:**
[figure not shown]
Consort flow diagram of recruitment and randomization

Participants from the EPIG will undergo an 18-week exercise intervention. The exercise sessions will be provided two times a week (each class approximately 1 to 1.5 h duration) and will be supervised by a qualified physiotherapist or an accredited exercise physiologist. Each session will consist of 5 to 10 min warm-up exercises, followed by 45 to 75 min on the equipment stations, and will conclude with 5 to 10 min of cool down exercises. The exercise classes will include 6 to 8 participants and will be circuit-based with the warm up and cool down exercises being performed in a group and the core session being carried out in training pairs. Participants will be performing exercises that focus on strength, balance, coordination, mobility and flexibility as detailed in Tables 1, 2, 3, 4 and 5. Exercisers will be paired in stations and an exercise session can include up to eight stations (See Table 6). The intervention program will be carried out at St Bernadette’s Community Respite House, with no cost to the participants.

**Table 1 Tab1:** Strength exercises to be performed using the senior exercise park with their respective levels of progression

Exercise	Description	Functional relevance	Progressions
Push-up bar	Participant pushes body up away from the bar and brings it down towards the bar.	Strengthens arms, back and core muscles.	Standing nearly perpendicular to the bar:
			Level 1 – Wide grip.
			Level 2 – Narrow grip.
			Level 3 – Wide grip standing on a 10cm high block*.
			Level 4 – Narrow grip, standing on a 10cm high block*
			Level 6 – Narrow grip, hand release.
			Level 7 – Narrow grip, front knee tucks.
			Level 8 – Narrow grip side knee tucks.
			Level 9 - Perform the push-ups with 1 hand. Hand on shoulder line.
Modified Pull-Ups	Participant pulls body up towards the bar.	Strengthens arms, back and core muscles.	Level 1–3 – Hands narrow (undergrip), increase distance from the bar (3 distances 3 distances determined by a line on the floor).
			Level 4–6 – Hands wide (undergrip) – increase distance from the bar (3 distances)
			Level 7–9 – Hands narrow (overgrip) – increase distance from the bar (3 distances).
			Level 10–12 – Hands wide (overgrip) – increase distance from the bar (3 distances).
			If the participant reaches RPE 4/10 again, the wooden 10-cm high block can be introduced on the exercise and all levels are repeated again.

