### Sample size

Power analysis was undertaken using previously published discharge data on the primary outcome measure - the BOOMER balance measure [26], and assuming an improvement of 3 points (reported as the minimum detectable difference [26]) and an effect size of 0.5. A sample size of 48 participants per group will be required for a power of 0.80 and alpha of 0.05. We will allow for 20 % dropout rate (this is a conservative estimate based on previous exercise programs with older people), and therefore will recruit 60 participants per group.

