Community-based exercise programs that focus on health and wellness for physically inactive community-dwelling seniors have been shown to be effective in reducing feelings of loneliness and social isolation [61]. After people retire, they are more likely to stay at home alone, watching television and reading newspapers, and consequently become sedentary in their lifestyle [62, 63]. The senior exercise parks may provide an opportunity for seniors to socialize more, improve their quality of life and, their physical and mental health. This novel method could be an option for them to exercise their bodies and minds in an enjoyable way through strength, balance and coordination exercises as well as simple activities to support a variety of activities of daily living.

The type of environment on which exercise-based therapeutic interventions are offered is vital for their success [60]. A study with post-menopausal women showed that indoor activities have been associated with negative feelings such as frustration, anger, sadness and anxiety whereas outdoor programs have been associated with positive feelings such as happiness, joy and pleasure [64]. Contributing to these findings, outdoor exercises were shown to improve mood and self-esteem in older people, and seniors tend to attend more to the outdoor sessions compared to the indoor ones [60]. However, outdoor sessions such as the one proposed by the senior exercise park program can be dependent on climate and seasonal conditions which has the potential to influence adherence [65]. The planned project will explore how participation can be affected by seasonal conditions.

The proposed intervention will use task-specific exercises (e.g. step and stair climbing, walking on unstable and uneven surfaces, etc.) which can be easily translated to older adults’ activities of daily living. In addition, senior exercise parks can be installed outdoors or indoors in public places such as community centres and parks free of charge to the public. While an intervention of this nature might comprise some financial and logistic engagement of the local councils and community organizations, this initiative could potentially be a cost-effective way to engage older individuals in a more active and healthier lifestyle.

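### Adherence by calendar season cannot by itself show a weather effect, because each season holds different participants at different programme weeks

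*Protocol article*

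**What the plan says.** The Feasibility section of the protocol article makes seasonal adherence one component of feasibility. It says the study will investigate whether "adherence would be influenced by weather conditions during the four seasons in Melbourne". The measure is then given as season boundaries: "Seasonal adherence will be recoded as adherence over Summer (December to end of February), Fall (March to end of May", with winter and spring defined in the same way. The Discussion returns to the question: "The planned project will explore how participation can be affected by seasonal conditions".

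The design facts that bear on this are elsewhere in the article:

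- **Programme length and frequency** (text under Fig. 1): "Participants from the EPIG will undergo an 18-week exercise intervention", and "The exercise sessions will be provided two times a week".
- **Entry** (Recruitment and randomization): "blocks of 12 participants will be recruited at a time", six to each group, over 14 months, to reach 60 per group.
- **Make-up sessions** (Fidelity monitoring): participants who missed more than eight sessions are asked to make them up after the 18 weeks, until they reach a minimum number of hours.
- **Overall adherence** (Feasibility): 100 % "adherence if participant attended 35 sessions or 9 sessions of social meetings". This denominator belongs to the whole programme. None is given for a season.
- **Other weather information** (Feasibility): sessions cancelled for rain, wind or heat are counted, and reasons for missed sessions go into the attendance diary.

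**The concern.** The stated aim concerns the effect of weather on attendance. The stated measure sorts attendance by calendar season. The two would match if every participant were seen in every season, or if each season held a similar mix of people at similar stages of the programme. Neither is assured here.

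Entry is staggered. When the trial opens, only early programme weeks exist. After the last block starts, only progressively later weeks remain. The seasons in between hold a mixture that depends on when blocks happened to start. A low figure for one season could therefore mean that its participants were further into the programme, or that its classes contained poorer attenders. A real weather effect could be masked in the same way.

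At stake is a feasibility conclusion about an outdoor programme in Melbourne, which could be read as evidence on when such a park is usable.

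**Working it through.** The article states no seasonal adherence figure, so there is none to reproduce. The check asks how far seasonal figures can differ when weather has no effect.

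**Step 1: seasons per participant.** 18 weeks × 7 = 126 days. For each of 365 possible start days, count the calendar seasons (as defined under Feasibility) that the 126 days touch. The result is two seasons for 230 start days (63 %), three for 135 (37 %), and never one or four. Make-up sessions can lengthen this somewhat.

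**Step 2: number of cohorts.** 60 exercise participants ÷ 6 per block = 10 exercise cohorts starting over 14 months (about 426 days). Each has 2 × 18 = 36 scheduled sessions.

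**Step 3: attendance falling with programme week, no weather effect.** Assumed, and not in the documents: attendance in week w = 0.95 × (1 − f × (w − 1)/17), with f the proportional fall from week 1 to week 18. Each session is assigned to its season and averaged. The gap is the largest minus the smallest seasonal figure. The formula is linear, so gap = 95 × f × (difference in mean programme week)/17 points, and halving f halves the gap.

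| Block starts | f = 0.20 | f = 0.10 (half) |
|---|---|---|
| Evenly spaced, over the 12 opening months | 1.4-2.4 points | 0.7-1.2 points |
| Random over 14 months: median (5th-95th percentile) | 4.8 (1.8-10.8) | 2.4 (0.9-5.4) |

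A second version started at 90 %, took the fall in absolute points, and placed the first and last blocks at the two ends of recruitment. With even starts it gave 1.0-1.5 points for a 10-point fall and 2.1-2.9 for a 20-point fall. With random starts the medians were 2.5 and 5.1. The two versions together support about 1-3 points with even starts and a median of about 2-5 with irregular starts.

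**Step 4: one case by hand.** Even starts from July, second version, 20-point fall. Mean programme week is 8.3 in winter and 10.4 in summer.

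- Winter: 90 − 20 × (8.3 − 1)/17 = 81.4 %.
- Summer: 90 − 20 × (10.4 − 1)/17 = 78.9 % (79.0 % before rounding the mean week).

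The gap of about 2.4 points falls on the winter-summer contrast, with no weather effect in the model.

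**Step 5: no fall, but participants differ.** Attendance is constant over weeks, with an assumed between-participant SD of 10, 15 or 20 points and even starts. The median gap is 3.1, 4.3 and 5.5 points (2.5th-97.5th percentile 0.9-6.6, 1.2-9.2 and 1.7-12.7).

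**Step 6: null case.** With no fall and no difference between participants, the gap is 0.

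In the models of steps 3 and 5, comparing seasons at equal programme week, or within participants respectively, gives 0 by construction.

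**The case against.** The strongest reply is that the article gives only season boundaries. It states no pooling, test or contrast, and the comparison may be set out in an analysis plan that is not shown. This stands in part. A reader might infer that the plan commits to comparing crude pooled percentages. The text does not say so, and nothing in it rules out an adjusted analysis of the same diary data. What remains is that the article states a question about weather and pairs it with a measure that cannot answer it alone.

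A second reply concerns size. It is tempting to take "We will allow for 20 % dropout rate" as the plan's own attendance decline and to announce spurious differences of 2 to 10 points. The documents do not support that. The 20 % is a sample-size allowance, described there as conservative, and it says nothing about when people leave. Feasibility also lists retention separately from adherence. If seasonal adherence is computed only among those still enrolled, withdrawal alone creates no gap of this kind. The upper end also needs irregular starts, and a largest-minus-smallest difference over four seasons is never negative, so some gap is expected by chance.

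Third, although stations and set times increase over the weeks (Tables 7 and 8), intensity is individually adjusted to a perceived-effort band. Rising demands are therefore a possible reason for falling attendance, not an established one.

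Finally, weather cancellations and reasons for absence are recorded, and interviews explore barriers to participation. These bear on the weather question more directly than season does, but they do not remove the confounding from the seasonal percentages.

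**Conclusion.** The point holds in a limited form. From the documents alone, no participant's 18-week programme covers all four seasons, and each season holds different cohorts at different programme weeks. Differences between crude seasonal figures therefore mix season with time in programme and with participant.

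The size is conditional on a 10-20 % fall in attendance over the programme, which is an assumption. On that basis the gap with no weather effect is about 1-3 points with evenly spaced starts. With irregular starts the median is about 2-5 points and the 95th percentile about 5-11. Differences between participants alone could produce gaps of similar size. If attendance varies neither by week nor by participant, the gap is zero.

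This is a minor point about a feasibility measure. It does not touch the primary outcome or the comparison of the randomised groups.

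**What to change.** Keep the raw seasonal percentages as description, each shown with its mean programme week and the number of classes that contribute.

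Base any statement about season on a session-level analysis of exercise-group attendance: attended yes or no for each session held, with season and programme week as fixed effects and participant (within class) as a random effect. Within one block, programme week and calendar time move together, so the separation of the two depends on blocks that started at different times. The report should say so.

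Report weather cancellations and weather-related reasons for absence alongside. Count make-up sessions separately, so that an absence in one season does not reappear as attendance in the next.

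Session attendance and reasons for absence are already kept in the diary, so no new data collection is needed. The cost is a short analysis statement, slightly more analysis, and wider intervals for the season effect. Those intervals reflect how little ten cohorts can say about four seasons.

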### Community partner organizations

An important aspect of projects of this nature is the identification of the community partner organizations that can help with personnel, infrastructure and logistical matters needed for its successful running. A key element of the design of this project is to conduct it in the community and therefore create a better platform for research translation. Therefore, a number of community organizations with a focus on older people’s health promotion and specialised care were approached. These community organizations were mainly selected based on the nature of the work they have been involved in with this specific population group. Two community organisations: Catholic Homes and Gateway Social Support Options have partnered to collaborate in this research project. Catholic Homes provided the infrastructure and land for the equipment installation and allow for the exercise session to be conducted in the community setting. Gateway Social Support Options is a community-based organisation with over 200 older people living in the western suburbs of Melbourne. Gateway Social Support Options will provide access to its members for participant recruitment.

### Exercise park

The senior exercise park used on this project was provided in-kind by Lappset (Fig. 2) and it was installed at the St Bernadette’s Community Respite House in Sunshine North. The exercise park consists of a number of components and stations that aim to work on the following aspects of physical performance: upper body mobility and fine motor skills, balance and coordination, lower limb and upper limb strength, stretching and flexibility (Tables 1, 2, 3, 4 and 5).

**Fig. 2 Fig2:**
[figure not shown]
Lappset’s exercise park for senior population

### Familiarisation and exercise intensity

A familiarisation session will be organised for each participant prior to commencement of the exercise program. The exercises will follow the guidelines of the Australian Position Statement of exercise for falls prevention [57]. Participants will be introduced to the 10-point Borg Rating of Perceived Effort (RPE) scale [58] at their familiarization session.

The initial level of the exercises difficulty will be tailored to the capabilities of the participant with the primary consideration of safety. Adjustment of the exercises (i.e. increase in intensity and difficulty) will be made based on the participant individual progression. RPE will be used to determine the intensity of each exercise where participants will be encouraged to exercise with a RPE between 4 and 7/10. New exercises will be gradually introduced to the participants every 1–2 weeks (See Table 7). A participant will progress to the next level of exercise when an RPE of below 4/10 (‘too easy’) will be reported (Tables 1, 2, 3 and 4).

**Table 7 Tab7:** Order of progression and introduction of new exercises for the 18 weeks of intervention

Week number	Exercise 1
1 and 2	Stations 1 to 5
3 and 4	Stations 1 to 6
5 and 6	Stations 1 to 7
7-18	Stations 1 to 8

### Individual and group exercise progression

Each station will include two exercises and will be performed twice by each participant. Two participants will be allocated in each station such that each participant will perform one at a time and will swap over (See Table 6). However, a participant can be exercising only with their exercise supervisor in case there is an uneven number. Participants will have different pairs and exercise supervisors on each session to stimulate social interaction. Participants will be given a resting period of 30–60 s which will be adjusted according to program progression as detailed in Table 8. The duration of each exercise will also increase based on program progression (Table 8). Rest periods between exercises will be used to discuss about difficulties and to provide further feedback. Participants will be allowed to have as many breaks as necessary to keep them performing the exercises with good technique and proper form. As some exercises such as step-ups on platform, ramp + walking through a net, and taps onto a platform can be more challenging to some participants due to the platform height, wooden blocks (L 70 cm x W 40 cm x H 10 cm) will initially be used for these participants. The same blocks will be used to make some exercises such as push-ups, pull-ups and sit to stand a bit more challenging to participants (Fig. 2).

**Table 8 Tab8:** Set time and rest for exercise progression for the 18 weeks of intervention

Week number	Set time	Rest time
1 to 2	60 s	60 s to change over and rest
3 to 8	60 s	30 s change over and rest
9 to 14	75 s	30 s change over and rest
15 to 18	90 s	30 s change over and rest

